### Statistical methods

No method will be planned to account for multiplicity.

### Interim analyses

No interim analysis will be performed.

### Statistical methods

**
*Adjusted analyses.*
** It will be specified in the SAP which confounders adjustments will be made for (
*e.g.*, age, pre-existing smallpox vaccination, extent of lesions,
*etc.*).

### Statistical method

**
*Analysis population.*
** All eligible participants will be included in the final analysis,
*i.e.*, the final analysis set will be the overall population of enrolled participants (prospective and retrospective, with positive mpox PCR).

**
*Method to account for missing, unused or invalid data.*
** The number, timing and pattern for missing values will be detailed for each outcome measure. For missing primary time-to-event outcome:

The patients who are lost to follow-up or withdrew from the trial and who did not experience the event will be censored at their lost to follow-up or withdrawal datePatients who died before experiencing the event will be censored at day 14If the patient is hospitalized, the event will be censored at hospital discharge day, whereas if the patient is an outpatient, the event will be censored at the last available date in the medical assessment formsIf the outcome is still missing, it will be searched in the Patient Self-Assessment Surveys (PSA)

For the four-point clinical scales at day 14 and day 28, missing data will be imputed by using the last observation carried forward (LOCF) method for “Death” and “All lesions are completely resolved and no serious complications” modalities. Missing outcomes will be searched as done for the primary endpoint.

Endpoints still missing after these recovery steps will remain missing in the analyses.

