### Early discontinuation and withdrawal of participants

Throughout the duration of the study, participants have the option to withdraw prematurely for various reasons, including but not limited to:

If a presumptive case enrolled in the study tests negative for MPXV, they are withdrawn.Participants may perceive certain adverse events (AE) as intolerable, leading to their withdrawal.Inability to adhere to the study procedures can also be a reason for withdrawal.Participants have the autonomy to decide to withdraw from the study.In some cases, the clinician may make the decision to withdraw a participant.

The study design provides participants with three withdrawal options, which are as follows:

1/ Participants can choose to withdraw from active follow-up and further communication. However, they allow their direct care team, acting on behalf of the study, to continue accessing their medical records and relevant hospital data that is routinely recorded as part of standard care. This data is essential for data collection on the electronic case report form (eCRF).

2/ Participants have the choice to withdraw from the study while permitting the retention of data and samples obtained up until the point of withdrawal. These retained data and samples will be used for analysis in the study, but no additional data or samples will be collected after the withdrawal.

3/ Participants may opt to completely withdraw from the study, including the request to remove the data and samples collected up until the point of withdrawal. In this case, the data and samples already obtained will not be utilized in the final study analysis.

The eCRF records both the type of withdrawal and the reason for withdrawal, ensuring proper documentation and tracking of participant decisions and the underlying motivations for their withdrawal from the study.

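### The censoring rule for withdrawals ignores the option that keeps medical-record data coming in, so known non-resolution after withdrawal can be dropped while a resolution from the same records counts

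*Protocol article*

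**What the plan says.** The rule is in the protocol article under *Statistical method*, paragraph *Method to account for missing, unused or invalid data*. The list opens with "For missing primary time-to-event outcome". Its first item states that those lost to follow-up, or who "withdrew from the trial and who did not experience the event will be censored at their lost to follow-up or withdrawal" date. Later items censor inpatients at discharge and outpatients at the latest date on their medical assessment forms, and then search the participant self-assessment surveys if the outcome is still missing. No item mentions the type of withdrawal.

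The section *Early discontinuation and withdrawal of participants* defines three options:

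- **Option 1:** "Participants can choose to withdraw from active follow-up and further communication". The care team is still allowed "to continue accessing their medical records and relevant hospital data that is routinely recorded as part of standard care", and the section calls these data essential for completing the eCRF.
- **Option 2:** data and samples up to withdrawal are kept, but "no additional data or samples will be collected after the withdrawal".
- **Option 3:** full withdrawal, after which "the data and samples already obtained will not be utilized in the final study analysis".

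The same section says that the eCRF captures both the type of and the reason for withdrawal.

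Under *Outcomes*, lesion resolution is followed to day 14 at most. *Statistical method* summarises it by Kaplan-Meier curves, the median and the proportion resolved at day 14, overall and by treatment status.

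**The concern.** Censoring at withdrawal suits option 2, where nothing is known afterwards. It is irrelevant to option 3, whose data are not analysed. It does not suit option 1, which exists so that information keeps arriving.

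The rule applies to participants without the event. Under option 1 that condition is judged on records that run past withdrawal. A resolution in those records means that the participant had the event. Active lesions in those records mean no event, and the rule then moves the censoring time back to withdrawal. Later events stay and later event-free time goes. Whether a participant stays in the risk set after withdrawal would then depend on the outcome, which Kaplan-Meier estimation does not allow for. The error is towards too much resolution at day 14.

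The article also leaves two possible dates for the same person. An option 1 outpatient who withdraws on day 7, with a day 14 form completed from the notes, is censored on day 7 by the first item and on day 14 by the outpatient item. No order of precedence is given.

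**Working it through.** **The article's own figures.** It states no withdrawal rate, event rate or power figure for this point, so there is nothing to reproduce. The check is one of logic, followed by illustrations of size.

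**Step 1: the rule against each option.** Take a participant who withdraws on day 7 with lesions still active.

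| Option | Known after day 7 | First censoring item, read literally |
|---|---|---|
| 1, records show resolution on day 12 | event on day 12 | event counted on day 12 |
| 1, records show active lesions on day 14 | no event to day 14 | censored on day 7; seven event-free days lost |
| 2 | nothing | censored on day 7, as it should be |
| 3 | data removed | not analysed |

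The asymmetry arises only under option 1. The survey search does not repair it. Option 1 participants have ended communication with the study, so later surveys are not to be expected, and the search step does not name the medical records.

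**Step 2: hand calculation (all inputs assumed).** Of 100 participants, 80 are unresolved after day 7 and 40 of these resolve by day 14. The true day 14 resolution is 1 - 0.80 x 40/80 = 60.0%. Suppose k of the 80 take option 1 on day 7 and half of them resolve by day 14. The k/2 who do not resolve leave the risk set and all 40 events stay:

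unresolved at day 14 = 0.80 x (80 - k/2 - 40) / (80 - k/2)

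- k = 4 (5% of those at risk): 0.80 x 38/78 = 0.390, resolution 61.0%
- k = 8 (10%): 0.80 x 36/76 = 0.379, resolution 62.1%
- k = 10 (12.5%): 0.80 x 35/75 = 0.373, resolution 62.7%
- k = 16 (20%): 0.80 x 32/72 = 0.356, resolution 64.4%

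The last two need a high share of option 1 withdrawals, all on one day.

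**Step 3: simulation over a wider range (all inputs assumed).** Each scenario had 400,000 participants and a constant daily chance of resolution h = 1 - (1 - p)^(1/14), with p = 50%, 70% or 85% by day 14. A share of 2%, 5% or 10% of all participants was assigned an option 1 withdrawal day, uniform from day 2 to day 13. Those already resolved by then are unaffected. Withdrawal was either unrelated to healing, or withdrawers healed at half the daily rate. The entries are the error in the Kaplan-Meier day 14 resolution, in percentage points, as a range over the three values of p.

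| Option 1 share | Records ignored, unrelated | Records ignored, half rate | Events only from records, unrelated | Events only from records, half rate | Records used for both |
|---|---|---|---|---|---|
| 2% | 0.0 | +0.2 to +0.3 | +0.2 to +0.3 | +0.4 to +0.5 | 0.0 |
| 5% | 0.0 | +0.5 to +0.7 | +0.4 to +0.7 | +1.0 to +1.1 | 0.0 |
| 10% | 0.0 | +1.0 to +1.4 | +0.9 to +1.4 | +1.9 to +2.3 | 0.0 |

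The literal reading (events only from records) overstates resolution even when withdrawal has nothing to do with healing. Using the records to day 14 for everyone on option 1 removes the error in every scenario.

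**The case against.** The strongest reply is that the rule was never meant for option 1. The list is introduced as dealing with a missing outcome, and a participant known to have active lesions on day 14 is arguably not missing. Option 1 is worded as leaving active follow-up, options 2 and 3 as leaving the study, and the censoring item speaks of leaving the trial, which fits option 2 best. The outpatient item could already give option 1 outpatients a sensible date. Nothing tells the analyst to accept events from the records and refuse non-events. The article also says that it only summarises the analysis, with details to follow in the SAP.

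This makes the text ambiguous but does not exempt option 1. The article presents all three routes as withdrawal options, and a participant with no event meets the stated condition whatever the records say about day 14. The outpatient item competes with the first item and does not override it. Deferring detail to the SAP does not remove the point either, because the article itself fixes the censoring date.

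Three parts of the objection do stand:

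- A reader might infer that known day 14 status in general is thrown away. The text does not say so; the loss is clear only for known non-resolution.
- A reader might infer that censoring must depend on outcome. If the records are ignored for everyone, that requires withdrawal to be related to healing. The listed reasons, such as "Participants may perceive certain adverse events (AE) as intolerable, leading to their withdrawal", make this plausible but do not establish it.
- The number exposed is limited. From January 2023 participants were recruited retrospectively, and anyone who consents after day 14 cannot withdraw within the 14-day window.

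**Conclusion.** The point holds in a limited form. The article sets one censoring date for all withdrawals, does not reconcile it with option 1, and gives a competing date for outpatients without saying which prevails. Read literally, the rule favours resolution in the primary analysis.

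The effect is probably small: about 0 to +2 percentage points on day 14 resolution (at most +2.3 in the scenarios run), assuming that 2% to 10% of participants take option 1 within 14 days and that withdrawal days are spread over that period. It is zero if records are ignored for everyone and withdrawal is unrelated to healing. The true rate is not given, so the size cannot be settled from the article.

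A reader might go further and expect a larger bias in the antiviral group, since only treated participants can react to a drug and the group is small (55 + 7 + 2 = 64 of 601 in the *Discussion*). The article does not support this as a finding. The withdrawal reason concerns adverse events in general, *Harms* collects them in treated and untreated participants alike, and no withdrawal rate by group is given. An imbalance is possible, not shown.

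**What to change.** Rewrite the first censoring item so that it depends on the withdrawal type already held in the eCRF:

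- **Option 1:** follow through the medical records to resolution or day 14. If neither is documented, censor at the last record-based assessment of lesion status. Apply the same data cut to events and non-events.
- **Option 2:** censor at the last lesion assessment on or before withdrawal.
- **Option 3:** excluded, as the withdrawal section already states.

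Add one sentence saying whether this item or the inpatient/outpatient item prevails when they give different dates.

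This is a free improvement: protocol or SAP wording and minor programming. It needs no new data, because option 1 participants have already agreed to the use of their records. Settling it before the analysis also removes a choice that could otherwise be made after the outcomes are seen.

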### Outcomes

**
*Primary outcome measure.*
** The primary outcome measure of this study is the participant’s time to lesion resolution without any serious complications. Lesion resolution is the first day on which all lesions are resorbed, scabbed or desquamated and mucosal ulcers healed. Lesion resolution is assessed until a maximum of 14 days since the date that the diagnostic sample is taken (for participants who do not receive mpox-specific antiviral treatment) or the day of treatment initiation (for participants who receive mpox-specific antiviral treatment).

**
*Secondary outcomes.*
** Secondary outcome measures evaluate clinical and virologic outcomes. Clinical outcomes are assessed on the basis of:

1. Clinical status on day 14 and day 28 according to a four-point ordinal scale assessed by a physician or a study nurse. The ordinal scale is a) all lesions are resolved and no serious complications, b) active lesions and no serious complications, c) serious complication and/or hospitalization due to mpox, or d) death.2. Evidence of recrudescence or relapse at day 60 and day 180.

*Note:* A "serious complication" is any complication associated with a Serious Advent Event (SAE) that is life-threatening, results in hospitalisation, prolongation of existing hospitalisation, disability, incapacity, or a congenital anomaly; or any other complication that is considered medically significant.

Virologic outcomes in Tier 1 are assessed on the basis of:

1. Change from baseline in mpox virus DNA levels in throat swabs on days 4, 8, 14 and 28.2. Change from baseline in mpox virus DNA levels in blood on days 4, 8, 14 and 28.3. Presence of mpox virus DNA in lesion swabs on days 4, 8, 14 and 28.

The study also assesses the number and type of SAEs, Suspected Adverse Reactions (SARS) and Suspected Unexpected Serious Adverse Reactions (SUSARs) within 28 days of enrolment.

Pregnancy outcomes defined as the final known health status of the mother and child are evaluated in any participants who are pregnant during the course of the study.

**
*Exploratory outcomes in Tier 2 and Tier 3.*
** Further virologic and immunological outcomes are also evaluated in France under this protocol to learn more about viral transmission, humoral and cellular immune responses. The outcome measures are as follows:

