### Data collection methods

All data are recorded by the clinical and study teams directly on the REDCap (version 13.1.30)
^
9
^ electronic Case Report Form (eCRF) for each timepoint as defined in
Table 1.

**
*Demographics and medical history.*
** Data relating to the participant’s demographics and medical history are collected at baseline. Demographic includes sex at birth and ethnic group. Medical history includes data on comorbidities, results of pregnancy and HIV tests, data on signs and symptoms experienced by the participant between the collection of mpox diagnostic sample and the point of consent, and details of potential AEs and SAEs occurring between the collection of mpox diagnostic sample and the point of consent.

**
*Medical assessments.*
** Medical assessments are undertaken at baseline, and D14, 28, 60, and 180. These assessments can be conducted in person,
*via* video link or telephone. The data collected include the participant’s signs and symptoms, any treatment they may be receiving for mpox, AEs and SAEs details.

**
*Biologic sampling.*
** Baseline samples are the participant’s diagnostic samples that may have been collected under routine care before the participant signed the consent form. Blood* (~0.5ml to 20ml depending on local collection procedures), two lesion swabs and one throat swab are collected at D4*, 8*, 14, 21* and 28 where feasible to do so and permitted under local and national regulations–the asterisk (*) denotes procedures only for hospitalised subject; day 21 and 28 sampling only if day 14 sample is still positive.

Where local capacity limits sample collection, sites should prioritise the collection of D14 and 28 samples. All samples are tested by PCR only conducted in local laboratories in each participating country.

In Tier 2 in France, in addition to the sampling covered in Tier 1, additional samples of mucosa, saliva, anus, urine, semen or vaginal secretions, and blood are collected at baseline, D8, D14, D28, D60 (in case of oral, genital or anal lesion) and D180 (only if sample is positive at D60).

In Tier 3 in France, in addition to the sampling covered in Tier 1 and 2, additional samples of blood are collected at D28, D60 and D180.

Samples in Tier 2 and 3 are tested as in
Table 2.

**Table 2. T2:** Tests by sample type.

TIER	Test	Sample							
		Lesion	Throat	Mucosal lesion	Saliva	Anus	Blood	Urine	Semen or vagina secretion
1	PCR	X	X				X		
1&2	Bacterial STIs detection		X			X	X	X	

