## Data management

### Source data

Source documents serve as the initial records of data and are used to obtain participants' data for the electronic case report form (eCRF). These source documents encompass a variety of materials such as hospital records (including medical history and medication details summarized into the eCRF), clinical and office charts, laboratory and pharmacy records, diaries, microfiches, radiographs, and correspondence. If the eCRF is the sole place where data is originally recorded without any other written or electronic records, the entries in the eCRF are considered source data.

In this study, primary data collection occurs through two main methods:

(i) Study staff at participating sites complete electronic case report forms on enrolment, during scheduled study visits, daily for in-patients, and whenever laboratory results become available.

(ii) Participants complete an online questionnaire daily during the first 14 days of the study (or while they are in the hospital) and at specific time points (D21, D28, D60, and D180).

The data entered in the electronic case report forms and the online questionnaire are stored in separate REDCap databases.

To ensure data quality, automatic data checks are programmed into the REDCap systems, alerting users during data entry to minimize missing, inconsistent, or erroneous data. Study sites are responsible for reviewing the data entered into the case report forms for their respective participants.

Centralized monitoring of all data collected in the study is conducted by the University of Oxford. This monitoring involves evaluating data compliance with the study protocol and assessing accuracy, as outlined in the study-specific Monitoring Plan. When issues are identified, queries are triggered to be resolved by the respective sites. If any issues are detected in the Participant Self-Assessment data, the study site is notified to communicate with the participant if necessary.

On-site monitoring may be necessary if serious or repeated non-compliance with the protocol is identified through centralized monitoring. Local or regional coordinating centers will carry out this on-site monitoring.

The REDCap database is hosted at the University of Oxford for a minimum of 25 years following completion of the study.

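### Inpatients with a missing primary outcome are censored at discharge but outpatients at their last assessment; read literally, this drops later lesion status for inpatients only and can bias the D14 resolution estimate

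*Protocol article*

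**What the plan says.** All places are in the protocol article.

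- **Endpoint (Outcomes).** The primary outcome is "time to lesion resolution without any serious complications". The horizon is fixed: "Lesion resolution is assessed until a maximum of 14 days since the date that the diagnostic sample is taken", or since treatment start for patients given an mpox antiviral.
- **Missing primary outcome (Statistical method, paragraph on missing, unused or invalid data).** For inpatients, if "the patient is hospitalized, the event will be censored at hospital discharge day". For outpatients, "the event will be censored at the last available date in the medical assessment" forms. Patients "who died before experiencing the event will be censored at day" 14. As the last step, if the outcome is still missing, "it will be searched in the Patient Self-Assessment Surveys (PSA").
- **Planned follow-up.** Under Data collection methods, "Medical assessments are undertaken at baseline, and D14, 28, 60, and 180", in person, by video or by telephone. The four-point clinical status, which separates resolved from active lesions, is recorded at D14. Table 1 marks the D14 medical and outcome assessments as priority timepoints. Under Source data, "Participants complete an online questionnaire daily during the first 14 days of the study", and the survey covers lesion status.
- **Analysis.** Kaplan-Meier curves, the median and the D14 resolution proportion are reported overall and by treatment status, and treatment effects come from a Cox model. The choice of confounders is left to the SAP.

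**The concern.** Discharge ends the stay, not the follow-up. A participant who leaves hospital on day 5 is still due a D14 assessment and daily surveys. Taken at its word, the inpatient clause sets the censoring date at day 5 whatever those sources show, while an outpatient with the same lesion history is censored at the last assessment, which may be D14. No reason is given for the split.

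Two things are at stake. First, Kaplan-Meier and Cox assume that patients censored on a given day have the same prospects as those who remain. Discharge plausibly depends on improvement, so that assumption is doubtful for inpatients. Second, the order of the steps is unclear. The survey search follows the assignment of censoring dates and applies only if the outcome is still missing, so a reader cannot tell whether an inpatient already censored at discharge is ever searched for.

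A related inconsistency concerns serious complications. The endpoint requires resolution without one, and the definition of a serious complication includes one that results in hospitalisation. Patients who can no longer have the event may therefore be censored at discharge as if they still could, whereas deaths stay in the risk set to D14.

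**Working it through.** The protocol gives no bias figure, hospitalised share or missing share, so there is nothing to reproduce. I separate three readings and then size them under stated assumptions.

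**Readings**

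1. Every inpatient unresolved at discharge is censored there; nothing later counts.
2. Resolutions recorded later count, but patients without one by D14 are moved back to discharge.
3. Only inpatients with no record after discharge are censored there.

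**Hand example.** Ten inpatients are all discharged on day 5. Five resolve on separate days between 8 and 13, and five have active lesions recorded at D14.

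- Common last-known-status rule: 1 − (9/10)(8/9)(7/8)(6/7)(5/6) = 1 − 5/10 = 50%. The same ten as outpatients assessed at D14 also give 50%.
- Reading 1: no events, and nobody is at risk after day 5, so the D14 proportion cannot be estimated.
- Reading 2: five leave at day 5, then 1 − (4/5)(3/4)(2/3)(1/2)(0/1) = 100%.
- Reading 3: nobody lacks later data, so 50%.

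The discharge clause therefore differs from a last-known-status rule only when later data exist.

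**Cohort simulation** (3 runs of 40,000 patients per setting)

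- From the documents: 601 enrolled; 55 on tecovirimat, 7 on cidofovir and 2 on both, so 55 + 2 = 57 with any tecovirimat (57/601 = 9.5%); 14-day horizon.
- Assumed: 70% of outpatients resolve by D14 (Weibull, shape 2); inpatient hazard is 0.6 times that, so 1 − 0.30^0.6 = 51% resolve; no true treatment effect; hospitalised share, untreated/treated, is 5/20%, 10/40% or 20/60%; discharge is either tied to healing (at 30–90% of the resolution time) or independent of it (day 2–12). For reading 3, 20% of inpatients lack later data.

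Kaplan-Meier D14 resolution, overall / treated:

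| Hospitalised | Discharge | Full follow-up | Reading 1 | Reading 2 | Reading 3 |
|---|---|---|---|---|---|
| 5/20% | tied | 0.689 / 0.669 | 0.683 / 0.646 | 0.697 / 0.693 | 0.688 / 0.664 |
| 5/20% | independent | 0.688 / 0.671 | 0.696 / 0.698 | 0.705 / 0.726 | 0.690 / 0.675 |
| 10/40% | tied | 0.674 / 0.623 | 0.661 / 0.561 | 0.690 / 0.675 | 0.671 / 0.614 |
| 10/40% | independent | 0.675 / 0.626 | 0.692 / 0.673 | 0.710 / 0.744 | 0.678 / 0.633 |
| 20/60% | tied | 0.657 / 0.588 | 0.628 / 0.447 | 0.686 / 0.667 | 0.651 / 0.567 |
| 20/60% | independent | 0.656 / 0.588 | 0.686 / 0.653 | 0.722 / 0.785 | 0.661 / 0.593 |

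- Reading 1, discharge tied to healing: overall falls by 0.6, 1.3 and 2.9 points; treated falls by 2.3, 6.2 and 14.1 points.
- Reading 1, discharge independent: overall rises by 0.8, 1.7 and 3.0 points; treated rises by 2.7, 4.7 and 6.5 points. This is a pooling effect: slower-healing inpatients leave the risk set early.
- Reading 2: overall rises by 0.8 to 6.6 points.
- Reading 3: overall moves by at most 0.6 points and treated by at most 2.1.

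**Cox hazard ratio (true value 1).** With full follow-up, the unadjusted ratios are 0.94, 0.86 and 0.81–0.82; their distance from 1 reflects confounding by hospitalisation alone. Reading 1 with tied discharge gives 0.89, 0.74 and 0.57. Reading 2 gives 0.98–1.02, 0.93–1.03 and 0.90–1.05. Reading 3 moves the ratio by at most 0.04. Adjusted for hospitalisation, every reading stays between 0.99 and 1.02. The Kaplan-Meier shifts remain.

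**The case against.** The rule is introduced for a missing primary outcome and ends with a survey search. On the ordinary reading, a patient with active lesions recorded at D14 is not missing, and discharge is used only when nothing later exists. That is reading 3, and the effect is small. This stands as a possible reading, but the text does not restrict the clause to such patients. If that is the intent, the inpatient clause adds nothing to a last-known-status rule.

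A reader might infer that every participant has usable data after discharge. The documents do not support that. From January 2023 patients were recruited retrospectively, the survey starts only at study entry, and the eCRF may be completed from existing notes. For such inpatients the daily hospital assessments stop at discharge, so discharge may be the last known date.

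A reader might also infer that censoring is informative by construction, or that antivirals concentrate in inpatients. No discharge criterion is given, and antiviral use is described as varying with time, country and supply. Both are plausible, neither is stated.

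The handling of serious complications could be left to the SAP. That is fair as to detail. The point is only that the stated rules hold deaths to D14 while a hospitalised patient who can no longer have the event falls under discharge censoring.

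**Conclusion.** The point holds as a defect in a stated rule. Inpatients and outpatients are censored differently without a reason, the order of the recovery steps is unclear, and on the literal reading later lesion status is lost for inpatients only. The Kaplan-Meier D14 proportion is the most exposed result, chiefly in groups with many inpatients. The Cox contrast is exposed only if hospitalisation is not adjusted for, and that choice is left to the SAP; the protection from adjustment was checked only with no true treatment effect.

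It does not follow that the primary estimates are certainly biased, or biased in a known direction. The shift is downward if patients about to heal are cut at discharge, and upward if known non-resolvers are removed there. Taking inpatients alone with a true 50% (assumed Weibull, shape 2, and mean stays of 4, 6 and 8 days) yields 85–100% on reading 2 and 6–18% on reading 1 when half of patients leave 1–5 days before resolving. Those extremes belong to mutually exclusive readings. Reading 1 with independent discharge gives 49–50% in the same patients, so no bias among inpatients themselves.

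For the whole cohort, the shift is about 0.5 to 3 points downward when all inpatients are cut and discharge is tied to healing. The treated group can move more, and little changes if few inpatients lack later data. All of this rests on assumed hospitalised shares, healing times and discharge patterns. The study is mainly descriptive, but the affected quantity is its primary outcome, so the rule should be settled before analysis.

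**What to change.** Replace the inpatient/outpatient split with one rule for every patient:

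1. Search all available sources first: D14 and other medical assessments, hospital records and self-assessment surveys.
2. If no resolution is found, censor at the last date on which lesions are known to be unresolved, at most D14 on the patient's own clock (diagnostic sample or treatment start). For a retrospective inpatient with no later data, this remains the discharge date.
3. Treat patients whose serious complication rules out the event as deaths are treated: no event, held in the risk set to D14.

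Report how many inpatients and outpatients are censored before D14, by treatment status, and add a sensitivity analysis for dependent censoring, such as inverse-probability-of-censoring weights or best and worst cases.

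The cost is a change of wording and of derivation code. It needs no new data collection, since it uses whatever the scheduled assessments, surveys and notes already hold.
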